#### ○ Early termination of the clinical trial (for a participant)

1. During the clinical trial, if symptoms improve and, based on both the participant's personal request and the judgement of the clinical trial physicians, it is determined that no further treatment is necessary, the clinical trial may be **terminated early** for that participant.
2. Participants whose clinical trial participation is terminated early for this reason are **not** included in the discontinuation/withdrawal group and are considered to have been **fully compliant with treatment**.

---

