## 12. Criteria for early termination of the clinical trial

If, during the conduct of the clinical trial, a **serious adverse event (SAE)** occurs that may have a serious impact on participant safety or on the progress of the trial:

- The investigator may terminate the participation of the affected participant in the clinical trial at that time.
- If the serious adverse event is considered to be **related to the trial intervention**, **all clinical trial procedures will be suspended**.

Whether the affected participant will continue to participate in the clinical trial after the adverse event will be decided through discussion between the participant and the

research team. If the research team determines, on medical grounds, that the participant can no longer safely continue in the trial, participation may be **forcibly terminated**.

---

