#### 4. Exploratory efficacy outcomes

- From the end of the 4-week treatment period until the 12-week follow-up, the following are investigated and compared between groups as exploratory outcomes:
  - ① Whether additional **invasive procedures** for low back pain were performed
    - e.g., injection therapy such as **nerve blocks, radiofrequency ablation, or lumbar surgery**.
  - ② Whether **strong opioid analgesics** were used for pain control.
  - ③ **Rate of early termination of treatment** due to sufficient symptom improvement (based on the early-termination criteria).
  - ④ **Use of rescue medications**
    - Type, dose, and frequency of rescue medications (NSAIDs, muscle relaxants, etc.) are recorded and analyzed.

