### c. Exploratory efficacy analysis

Exploratory outcomes will be analyzed as follows:

- **Additional procedures/surgery after the study**
  - ▶ Evaluation of additional nerve block procedures or surgery after the end of treatment
    - Within 8 weeks after the end of the treatment period, it will be investigated whether participants received additional procedures for pain control (e.g., **nerve block procedures**, radiofrequency ablation) or underwent **lumbar surgery**. Based on these data, the **rate of additional procedures** will be evaluated.
    - If significant differences between treatment groups are identified, **post-hoc tests** will be performed.
    - Between-group comparisons of the rates of additional procedures or surgery will be conducted using the **Chi-square test** or **Fisher's exact test**.
    - *Additional procedure rate* =  

$$\left( \frac{\text{Number of patients who underwent additional procedures or surgery}}{\text{Number of patients who completed the study}} \right) \times 100$$
- **Rate of early termination of treatment**
  - ▶ Evaluation of the early termination rate

- Among participants whose treatment was completed early because they met the predefined criteria for **treatment completion prior to the scheduled end of therapy**, the **rate of early termination** will be evaluated for each group.
  - Between-group comparisons of the early termination rate will be conducted using the **Chi-square test** or **Fisher's exact test**.
  - *Early termination rate* =  

$$\left( \frac{\text{Number of patients whose trial participation was terminated early}}{\text{Number of patients who completed the study}} \right) \times 100$$
  - **Analysis of rescue medication use**
    - ▶ Analysis of rescue medication use
      - For each participant, information on the **type of rescue medication used**, **dose**, and **timing of administration** will be collected.
      - For each treatment group, the number of uses and total amount of rescue medication by drug type will be compared between groups using an **independent t-test**, or, if the normality assumption is not satisfied, a **Wilcoxon rank-sum test**.
- 

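### The exploratory early-termination rate is divided by study completers, so it moves with each arm's withdrawals and may not be a proportion at all

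*Protocol*

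**What the plan says.** Section 15, 2) c (Exploratory efficacy analysis) prints the early-termination rate as "Number of patients whose trial participation was terminated early" over "Number of patients who completed the study", times 100. The arms are to be compared by the Chi-square test or Fisher's exact test.

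The outcome itself is listed in section 14.1, item 4, as early termination of treatment "due to sufficient symptom improvement (based on the early-termination criteria"). The sentence above the formula carries a similar limit: "Among participants whose treatment was completed early because they met the predefined criteria for" completing treatment before its scheduled end.

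The term has two homes elsewhere:
- Section 9 (Early termination, for a participant) applies when symptoms improve and "it is determined that no further treatment is necessary". These participants are not counted as withdrawn and are treated as fully compliant.
- Section 12, whose heading also speaks of early termination, concerns serious adverse events: "The investigator may terminate the participation of the affected participant in the clinical trial at that time". Section 9 separately lists a serious adverse event that prevents continuation as a ground for discontinuation/withdrawal.

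The general rule in section 15 is that efficacy is analysed primarily in the full analysis set (FAS).

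**The concern.** Completing the study is an event after randomisation, in a trial where participants and treating clinicians know the allocation (section 7, 2)). A participant who withdraws has a known status for this outcome: treatment did not end because of improvement. Taking that participant out of the denominator raises the arm's rate, and raises it more in the arm that loses more people. The comparison is then no longer between the groups as randomised, and unequal withdrawal alone can make equal arms look different.

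The Protocol also does not say whether someone who stopped for improvement has completed the study. If not, the people in the numerator are absent from the denominator and the result is not a proportion.

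Finally, the numerator gives no reason for termination, although the outcome definition does.

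**Working it through.** **The plan's own figures.** The Protocol gives no expected early-termination rate. The arm size and dropout come from section 6, 3): n = 2 × (1.96 + 0.84)² / 0.96² = 17.01, rounded up to 18; 18 / (1 − 0.20) = 22.5, rounded up to 23 per arm. Both agree with the Protocol. Twenty per cent of 23 is 4.6, so about 5 withdrawals per arm are expected.

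**Formulas.** Let s be the share of randomised participants who stop for improvement and w the share who withdraw.
- Over all randomised: s.
- Printed formula, stoppers counted as completers: s / (1 − w).
- Printed formula, stoppers not counted as completers: s / (1 − w − s).

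**Equal true stopping, unequal withdrawal** (assumed: s = 20% in both arms, w = 10% against 30%).
- Over all randomised: 20% against 20%.
- Stoppers as completers: 0.2/0.9 = 22% against 0.2/0.7 = 29%.
- Stoppers not completers: 0.2/0.7 = 29% against 0.2/0.5 = 40%.

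**One arm at the planned dropout** (5 withdrawals of 23; 5 stoppers assumed).
- Over all randomised: 5/23 = 22%.
- Stoppers as completers: 5/18 = 28%.
- Stoppers not completers: 5/13 = 38%.

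**Range over other assumed splits**, with 6 stoppers in each arm of 23 (26.1% in both over all randomised):

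| Withdrawals by arm | Stoppers as completers | Fisher p | Stoppers not completers |
|---|---|---|---|
| 0 and 5 | 6/23 = 26.1% vs 6/18 = 33.3% | 0.73 | 6/17 = 35.3% vs 6/12 = 50.0% |
| 0 and 9 | 6/23 = 26.1% vs 6/14 = 42.9% | 0.47 | 6/17 = 35.3% vs 6/8 = 75.0% |

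**Beyond 100%.** If stoppers are not completers, 10 stoppers and 4 withdrawals among 23 leave 23 − 10 − 4 = 9 completers, and the rate is 10/9 = 111%. With 9 as the arm total, the non-event cell is 9 − 10 = −1, so neither named test can be run.

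**Numerator.** Set side by side, section 14.1 and the sentence above the formula restrict the outcome to improvement or to meeting the completion criteria. The formula has no such restriction, and section 12 applies the same label to stops after a serious adverse event. The responder definition in section 15, 2) d uses nearly the same phrase and does add symptom improvement as the reason.

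**The case against.** **Harm scored as benefit.** A reader might infer from the bare numerator that a termination for a serious adverse event would count as an efficacy success. The Protocol does not support that. Section 14.1 defines the outcome by symptom improvement, the sentence above the formula limits it to those meeting the completion criteria, and section 9 files serious-adverse-event stops under withdrawal. What stands is a missing qualifier and an overlapping term.

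**The more extreme reading.** Section 9 treats improvement stoppers as fully compliant and not withdrawn, and the per-protocol definition speaks of their treatment as completed. Counting them as completers is therefore the likelier reading, and the 38%, 40% and 111% results belong to the less likely one. No section settles the question, so a clarification is still needed.

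**False significance.** The stopping and withdrawal splits are assumptions. Under 20% stopping and 10% against 30% withdrawal, with stoppers as completers and 23 per arm, Fisher's test rejects in a little under 5% of trials, against about 2.5% with all randomised as denominator. That is within the nominal level. Among equal stopper counts with no withdrawals in one arm and up to 9 in the other, the smallest p is 0.007 (14/23 against 14/14), an extreme case. The objection stands: what suffers is the reported rate, and a spurious significant result will be rare.

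**Loose wording nearby.** The phrase restricting the evaluation to those who stopped early could be read as a rate of 100%, and section 14.1 introduces the outcome with "From the end of the 4-week treatment period until the 12-week follow-up, the following are investigated and compared between groups as exploratory outcomes", after scheduled treatment has ended. Neither changes the calculation: the formula is printed, and section 15 places the event before the scheduled end of therapy.

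**Conclusion.** The denominator is wrong as written. It drops known non-events, departs from the analysis set the Protocol uses for efficacy, and makes the rate depend on withdrawal. On the likelier reading the distortion is about 7 percentage points in the assumed scenarios (22% against 29%; 26.1% against 33.3%) and about 17 points if 9 withdrawals fall in one arm and none in the other. These sizes rest on assumed stopping and withdrawal figures. That the rate rises with withdrawal does not.

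It is an open question in the text, and not an established error, whether improvement stoppers are outside the denominator. The numerator is a wording gap, since the intent to count only improvement stops is clear. The effect is confined to exploratory rates in a 46-participant pilot; the primary analysis of low back pain does not use them.

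**What to change.** In section 15, 2) c:
- **Denominator:** all participants randomised to the arm. The FAS is not a substitute, because section 15 also requires at least one treatment and one post-baseline efficacy assessment, so some early withdrawals would again be dropped.
- **Numerator:** participants whose treatment ended early because of symptom improvement under section 9.
- **Separate reporting:** give terminations for serious adverse events and other withdrawals as their own counts by arm.
- **Terminology:** reconcile early termination across the two parts of section 9 and section 12, and state whether improvement stoppers count as having completed the study.

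Review the additional-procedure rate in the same section, which has the same completer denominator. It needs its own decision: a withdrawn participant is a known non-event for stopping because of improvement, but may have unknown status for procedures during follow-up.

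The cost is a wording change, with no new data. The reported rate will be lower than the printed formula would give, for example 22% in place of 28% with 5 stops and 5 withdrawals among 23.

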#### d. Classification of responders and non-responders and post-hoc analysis

- **Responder definition**
  - ▶ Classification of treatment responders and non-responders
    - Using the change in NRS for low back pain from baseline to each evaluation time point, the **minimal clinically important difference (MCID)** is defined as a **decrease of 2 points** on the NRS.
    - Participants who show a decrease of **2 points or more** on the NRS are defined as having achieved MCID and are classified as the **treatment responder group**.
    - Participants with less than a 2-point decrease are classified as the **non-responder group**.
    - In addition, participants whose trial participation is **terminated early due to symptom improvement** because they meet the early termination criteria are also included in the **responder group**.
- **Post-hoc analysis**
  - ▶ Post-hoc analysis based on responder classification
    - Using the above definition of responders and non-responders, appropriate **post-hoc analyses** will be performed by a professional

statistician to investigate differences in outcomes between groups according to response status.

---

### 3) Safety analysis

- For adverse events, the **number of events**, **number of affected participants**, **severity**, and **causal relationship with the intervention** will be summarized descriptively by treatment group. If necessary, **nonparametric methods** may be applied.
  - Vital signs, physical examination findings, and patients' subjective complaints will be comprehensively reviewed. For any parameters judged by the investigator to show **clinically meaningful changes**, statistical analyses may be performed as needed.
  - For continuous data, the **number of observations**, **mean**, **standard deviation**, **median**, **minimum**, and **maximum** will be presented by visit. Within-group changes will be analyzed using a **paired t-test** or **Wilcoxon signed-rank test**.
  - For adverse event data, between-group comparisons will be conducted using the **Chi-square test** or **Fisher's exact test**.
  - If clinically meaningful changes are observed and a comparison between groups is needed, methods such as **generalized estimating equations (GEE)** may be used to evaluate whether there are statistically significant differences between groups over time.
- 

## 16. Methods for reporting and evaluating adverse events

Following Chuna manual therapy, the expected adverse reactions include **worsening of pain at the treatment site**, **fatigue**, etc., and in rare cases **nerve injury** and **fracture** may occur. For ICT, possible adverse reactions include **skin irritation** at the treatment site, **burns**, **blistering**, and **discomfort after treatment**.

In this study, the scope of adverse events related to the study procedures is defined on this basis as follows:

- For **Chuna manual therapy**, adverse events include **worsening of pain**, **fatigue**, **fracture**, and **nerve injury**.
- For the **usual care group (ICT)**, adverse events include **burns**, **blistering**, and **worsening of pain**.

Adverse events that are clearly **unrelated to the study interventions** are **not** classified as serious adverse events for the purpose of this protocol. The methods for reporting and evaluating adverse events are described below and are adapted from the

standard procedures used in drug–intervention clinical trials, applying the same basic definitions and evaluation criteria.

The investigator must record **all adverse events** that occur during the clinical trial. In the case report form (CRF), the following must be documented for each adverse event:

- Symptoms and signs,
  - Duration (start date / end date),
  - Severity,
  - Course and outcome,
  - Seriousness,
  - Causal relationship to the clinical trial procedure,
  - Actions taken in relation to the adverse event.
- 

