**(2) Confirmation of adverse events such as subjective and objective symptoms:**

Performed at every visit after randomization

- The clinical trial investigator must record all adverse events and concomitant medications that occur during the trial.
- Adverse events and concomitant medications are recorded in the case report form (CRF). For adverse events, the following must be documented: the symptoms and signs of the event, duration (start date/end date), severity, outcome, seriousness, causal relationship with the investigational intervention, and any actions taken in relation to the adverse event.
- Symptoms or signs that were already present before participation in the clinical trial are not recorded as adverse events. However, if after enrollment there is any change in the frequency, severity, or extent of such symptoms or signs, they must be recorded as adverse events.
- For concomitant medications, the generic name, dose, period of administration, and reason for use must be recorded in detail (for specific evaluation methods, see **Section 18. Methods for reporting and evaluating adverse events**).

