## 1) Definitions

### (1) Adverse Event (AE)

An adverse event is any unfavorable and unintended sign, symptom, or disease that occurs in a participant who has received a clinical trial procedure, and **does not necessarily have a causal relationship** with that procedure.

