### (4) Serious Adverse Event (Serious AE)

A serious adverse event is an adverse event occurring in association with the clinical trial procedure that meets **any** of the following criteria:

- Death of the participant during the trial period.

- A life-threatening event (the participant is in immediate danger of death at the time of the event; this does not refer to hypothetical situations where the participant might have died if the event had been more severe).
- An event that requires hospitalization or prolongation of existing hospitalization (however, hospitalization for simple rest or convalescence does **not** constitute a serious adverse event).
- An event that results in persistent or significant disability or substantial disruption of the ability to conduct normal life functions.

Even if a situation does not fall strictly into one of the above categories, if it is judged that the situation has a **significant impact on the participant's comfort or health status**, the responsible physician and relevant experts will determine, based on medical judgement, whether the event should be considered a **serious adverse event**, and appropriate measures will be taken accordingly.

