## 2) Evaluation of adverse events

- In this clinical trial, adverse events include any undesirable and unintended signs or symptoms that were **not present before the start of the trial** and that newly appear during the treatment period, regardless of whether a causal relationship to the clinical trial procedure is established.
- All events that are expected adverse reactions to the clinical trial procedure (symptoms and signs, onset date, duration, etc.) must be fully and accurately recorded in the adverse event section of the CRF.
- The **severity** of adverse events will be graded by the principal investigator and sub-investigators according to a stepwise scale, with reference to **"4) Assessment of the relationship to the clinical trial procedure."**
- The **causal relationship** between the clinical trial procedure and the adverse event will be classified into **six categories** as described in **"4) Assessment of the relationship to the clinical trial procedure."**

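### Section 16 makes the seriousness of an adverse event depend on its causality, and its description of adverse events conflicts with other sections of the protocol

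*Protocol*

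**What the plan says.** **Seriousness.** The introduction to Section 16 says that events clearly unrelated to the interventions are not "classified as serious adverse events for the purpose of this protocol". Section 16, 1) (4) adds a second condition in its lead-in: "A serious adverse event is an adverse event occurring in association with the clinical trial procedure that meets" any of the listed criteria. The first of those criteria is "Death of the participant during the trial period"; the others are threat to life, hospitalisation, and lasting disability.

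Elsewhere seriousness and causality are handled as two judgements. Section 12 supposes an SAE that has occurred and then asks whether it is related ("If the serious adverse event is considered to be" related to the intervention, all trial procedures are suspended). Section 14.2 (2) and the Section 16 introduction each list seriousness and causal relationship as separate items to document. The Section 16 introduction also claims the same basic definitions as drug trials.

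**Scope of adverse events.** Section 16, 2) describes adverse events as signs or symptoms absent before the trial "and that newly appear during the treatment period, regardless of whether a causal relationship to the clinical trial procedure is established". The formal definition in Section 16, 1) (1) has neither limit: "An adverse event is any unfavorable and unintended sign, symptom, or disease that occurs in a participant who has received a clinical trial procedure". Section 14.2 (2) says of pre-existing symptoms that "if after enrollment there is any change in the frequency, severity, or extent of such symptoms or signs, they must be recorded as adverse events". The Section 16 introduction lists worsening of pain as an adverse event for both Chuna and ICT. Section 16, 3) requires recording over the whole trial period.

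**The concern.** Seriousness describes what happened to the participant; causality is an opinion about why. If the second decides the first, the SAE count stops being a count of outcomes and becomes partly a record of investigators' opinions. In this trial those opinions are not blinded: Section 7, 2) says that clinical investigators cannot be blinded, and Section 16, 4) gives them the causality classification. The judgement also takes effect before oversight starts, because the SAE reports and the IRB's SAE review cover only what has been called serious.

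The adverse event description raises a second problem. Every participant enters with low back pain, so worsening of that pain can never be a new symptom, yet it is the first expected reaction that Section 16 names for Chuna. Staff at the two sites could follow different paragraphs in good faith and record different things.

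**Working it through.** The point concerns definitions and the plan gives no figure to reproduce, so the check compares sections.

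**Step 1. Is seriousness tied to causality?**

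| Place in the protocol | Does SAE status depend on causality? |
|---|---|
| Section 16, introduction | Yes: clearly unrelated events are excluded |
| Section 16, 1) (4) | Yes: the event must be associated with the procedure |
| Section 12 | No: relatedness is judged once the event is already an SAE |
| Section 14.2 (2) and the item list in the Section 16 introduction | No: seriousness and causality are separate items |

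The first two rows cannot both hold with the last two. If every SAE were already procedure-related, the conditional in Section 12 would have almost nothing to decide. The protocol also has causality-based categories of its own, the adverse treatment reaction and the serious and unexpected adverse treatment reaction (Section 16, 1) (2) and (5)), so the SAE term does not need to carry causality.

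**Step 2. Can the exclusion be applied as written?** The causality scale in Section 16, 4) has six levels: certain, probable, possible, unlikely, conditional and unassessable. None is labelled unrelated. The text does not say whether an event rated unlikely counts as clearly unrelated, so the judgement that removes SAE status has no defined criterion. The two exclusions also differ in strength: the introduction removes only clearly unrelated events, while the definition asks for a positive association.

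**Step 3. What happens to one event?** Take a hospitalisation in week 3 that the investigator judges clearly unrelated.
- It meets the formal adverse event definition, which needs no causal link, and is recorded.
- It meets the hospitalisation criterion, but the introduction to Section 16 removes its SAE status.
- The immediate report to the principal investigator (Section 16, 7)), the 24-hour report to the sponsor and the report to the IRB (responsibilities of the principal investigator) are all written for SAEs, so they no longer apply to it.

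A death follows the same path. It stays in the data, since Section 16, 6) has a fatal outcome code, but not as an SAE.

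**Step 4. Which events count as adverse events?**

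| Event | Section 16, 2) | Other sections |
|---|---|---|
| Worsening of baseline back pain | Not described as an adverse event, because not new | Must be recorded: Section 14.2 (2); Section 16 introduction, for Chuna and ICT |
| New symptom in weeks 4 to 12 | Not described, because after treatment | Must be recorded: Section 16, 3); no time limit in Section 16, 1) (1) |

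Treatment lasts 4 weeks and the last assessment is at week 12 (Section 8, 4)). The share of scheduled follow-up outside the Section 16, 2) window is (12 − 4)/12 = 8/12 = 67%. This is a share of calendar time, not of events.

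**Step 5. A third window.** Section 16, 7) requires events within 7 days after the procedure to be reported even after the trial is complete. For a participant treated on schedule, 7 days after the last session is about week 5, well before week 12. How this clause relates to the whole-trial window is not stated.

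**Step 6. The CRF list.** The seven items under Section 16, 3) omit seriousness, which Section 14.2 (2) and the Section 16 introduction both require.

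**The case against.** **The exclusion is narrow.** It reaches only events that are clearly unrelated, and an adverse treatment reaction covers anything whose relation cannot be completely ruled out. Association with the procedure might be meant as timing rather than cause. The SAE definition also ends with a clause that lets physicians call other events with a significant impact serious. Some of this stands: related and doubtful deaths and hospitalisations remain SAEs under the introduction to Section 16. But a reading based on timing does not rescue the introduction, which is plainly about relatedness. The closing clause is discretionary and says nothing about unrelated events.

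**A reader might infer that deaths and hospitalisations go uncounted.** The document does not support this. Section 16 requires all adverse events to be recorded, the formal definition needs no causal link, a fatal outcome has its own code, and the safety analysis in Section 15, 3) counts adverse events without regard to seriousness. What is lost is serious status and SAE reporting.

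**A reader might infer that the narrow description in Section 16, 2) governs, so that worsened pain is hidden.** It does not clearly govern. It says that adverse events include such symptoms, not that they are limited to them, and four other places point the other way. Low back pain is also measured as the primary outcome at weeks 4 and 12. The conflict stands; the loss of events is conditional on staff following that paragraph.

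**A reader might infer that the arms are compared on different event lists, since Section 16 names different reactions for Chuna and for usual care.** This does not hold. The lists give reactions by procedure, are introduced as inclusive, and share worsening of pain. The between-group comparison in Section 15, 3) is not restricted to them.

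**Conclusion.** The seriousness part is wrong as written and needs correction. Section 16 twice ties SAE status to causality, against Section 12, against the separate recording items, and against its own claim to use drug-trial definitions. The effect is that a death or hospitalisation which an unblinded investigator judges clearly unrelated is recorded as an adverse event but is neither counted nor reported as an SAE.

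The adverse event scope is a secondary inconsistency to be reconciled. Only if Section 16, 2) is read as a limit and followed would worsened baseline back pain, and events in the 8 weeks after treatment (67% of scheduled follow-up), not count.

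The number of events affected in either case cannot be derived, because the protocol gives no expected event rates.

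**What to change.** 1. Delete the sentence in the Section 16 introduction that excludes clearly unrelated events from SAE status.
2. In Section 16, 1) (4), remove the phrase in the lead-in that ties the event to the procedure. Seriousness then rests on the listed outcome criteria, and causality is recorded separately on the existing scale.
3. Reword Section 16, 2) to cover any new or worsened sign or symptom, and set one collection window for both arms. That window must be reconciled with Section 14.2 (2), which starts at randomisation and speaks of changes after enrolment; with Section 16, 1) (1) and 3); and with the 7-day clause in Section 16, 7). A window starting at the first session would still not match Section 14.2 (2).
4. Add seriousness to the CRF item list under Section 16, 3).

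The cost is protocol wording, one CRF field if it is not already there, and a few more SAE reports. No visit or procedure is added.
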